## Abstract

**Background:**

In the Netherlands, absenteeism and reduced productivity due to work disability lead to high yearly costs reaching almost 5% of the gross national product. To reduce the economic burden of sick leave and reduced productivity, different employability interventions for work-disabled employees or employees at risk of work disability have been developed. Within this study, called 'CASE-study' (Cost-effectiveness Analysis of Sustainable Employability), five different employability interventions directed at work disabled employees with divergent health complaints will be analysed on their effectiveness and cost-effectiveness. This paper describes a consistent and transparent methodological design to do so.

**Methods/design:**

Per employability intervention 142 participants are needed whereof approximately 66 participants receiving the intervention will be compared with 66 participants receiving usual care. Based on the intervention-specific characteristics, a randomized control trial or a quasi-experiment with match-criteria will be conducted. Notwithstanding the study design, eligible participants will be employees aged 18 to 63, working at least 12 h per week, and at risk of work disability, or already work-disabled due to medical restrictions. The primary outcome will be the duration of sick leave. Secondary outcomes are health status and quality of life. Outcomes will be assessed at baseline and then 6, 12 and 18 months later. Economic costs will consist of healthcare costs and cost of lost production due to work disability, and will be evaluated from a societal perspective.

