
### Sample size

For the economic evaluation of the three newly developed employability interventions, the study sample size was pre-specified by the researchers and the developers of the particular interventions. For the sample size calculation of the existing 'Best Practices', we expect that a Hazard Ratio (HR) of 2.0 indicates a relevant difference in the average number of hours/days of lost work due to work disability between employees in the intervention group and employees in the control group after 18 months. This HR is based on findings of recent studies in occupational health care [25,52-55]. With a power of 80% at a 0.05 significance level, the sample size was calculated to be 120 employees [56]. Taking into account a dropout rate of 15%, 5% per follow-up measurement time, a total of 142 participants are needed. A dropout is defined as an employee who has not filled in the questionnaire at one or more measurement time-points.

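### The abstract's arm sizes (66 + 66 = 132) do not add to the 142 it states, and it applies the 142 to every intervention although the Sample size section derives it only for the two Best Practices

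*Protocol article*

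**What the plan says.** The abstract, under Methods/design, states one size for each comparison: "Per employability intervention 142 participants are needed whereof approximately 66 participants receiving the intervention will be compared with 66 participants receiving usual care".

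The Sample size section treats the two kinds of intervention differently. On the new ones it says: "For the economic evaluation of the three newly developed employability interventions, the study sample size was pre-specified by the researchers and the developers", and it gives no number. For the existing Best Practices it sets out a calculation. On the effect it says "we expect that a Hazard Ratio (HR) of 2.0 indicates a relevant difference". It then continues: "With a power of 80% at a 0.05 significance level, the sample size was calculated to be 120 employees". The dropout step follows: "Taking into account a dropout rate of 15%, 5% per follow-up measurement time, a total of 142 participants are needed".

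The section on the organisation of the CASE-study counts two Best Practices and three newly developed interventions. The Sample size section states neither an allocation ratio nor arm sizes. The split into 66 and 66 appears only in the abstract.

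**The concern.** Two statements in the abstract disagree with the calculation they summarise.

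First, the arm sizes do not add to the stated total, and they do not correspond to the total before or after the dropout allowance. Someone taking the recruitment target from the abstract cannot tell whether it is 132 or 142. The lower number, taken as the target, falls short of the article's own requirement.

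Second, a figure derived for two of the five interventions is presented as the requirement for all of them. The Discussion offers this design as the one to be applied to each intervention, and the organisation section says programmes were turned away for lacking the minimum number of participants. The article should therefore be clear about what that number is and which interventions it covers.

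**Working it through.** **Inputs**
- Abstract: total 142; arms about 66 and 66.
- Sample size section: HR 2.0, power 80%, significance level 0.05, 120 before dropout, 15% dropout, 142 after dropout, for the Best Practices.
- Organisation section: 2 Best Practices + 3 new interventions = 5.
- Assumed here: 1:1 allocation, as the abstract's equal arms imply, and a two-sided test, since sidedness is not stated.

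**1. The plan's own figure.** 120/(1 − 0.15) = 141.2, rounded up to 142. The step from 120 to 142 reproduces exactly.

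**2. Arm sizes.**
- 142/2 = 71 per arm recruited.
- 120/2 = 60 per arm after dropout.
- 66 + 66 = 132, and 142 − 132 = 10, or 7.0% of 142.

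**3. Can dropout explain 132?**
- As the number left from 142: loss 10/142 = 7.0%, not 15%.
- As the number enrolled to yield 120: loss 12/132 = 9.1%, not 15%.
- Partway through follow-up at 5% per measurement: 142 × 0.95 = 134.9 after the first (67.5 per arm) and 142 × 0.90 = 127.8 after the second (63.9 per arm).
- Other ways of inflating 120: 120 × 1.15 = 138, and 120/0.95³ = 140.0.
- 120 × 1.10 does equal 132, but no part of the article states a 10% allowance.

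None of the readings based on the stated dropout gives 66 per arm.

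**4. Consequence if 66 per arm were the recruitment target.** 132 × 0.85 = 112.2, so about 112 remain, against the required 120.

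Power is found by taking 120 as giving exactly 80% and letting events scale with the number remaining:
- z = (1.96 + 0.84) × √(112.2/120) − 1.96 = 2.80 × 0.967 − 1.96 = 0.75, so power is about 77%.

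The same check with whole events, using Schoenfeld's formula:
- Events needed = 4 × 2.80²/(ln 2)² = 65.3, rounded up to 66.
- 66/120 = 0.55, and 112.2 × 0.55 = 61.7 events.
- z = (ln 2 × √61.7)/2 − 1.96 = 0.76, so power is about 78%.

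The 0.55 is solved back from 120 and is not a design assumption in the article. The gap between 77% and 78% comes only from rounding 65.3 up to 66.

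**5. Scope, side by side.** The abstract attaches 142 to each employability intervention. The Sample size section attaches the calculation that ends in 142 to the Best Practices (2 of 5) and describes the other three as pre-specified elsewhere, without a number.

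**The case against.** Several points can fairly be made for the article.

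- **The abstract says approximately.** That could cover one or two participants, but not a gap of ten in a figure that the body of the article derives exactly. This defence fails.
- **142 may be right for all five.** The organisation section says the remaining five programmes can meet the minimal requirements, so a common minimum is possible. That section gives no value for it. The scope is therefore unclear and the article does not support the general statement, but 142 has not been shown to be wrong for the new interventions. This stands, and the point is worded accordingly.
- **The power loss is small and an upper bound.** Dropout is defined as missing one or more questionnaires, and the effectiveness analysis plans censoring and multiple imputation. Many dropouts would still contribute follow-up, so 77–78% describes the case where they contribute nothing. It also arises only if 66 per arm was really used as the target, which the article does not show. This stands.

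Stronger readings are tempting but unsupported:

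- A reader might infer that 80% power is claimed for every intervention. It is not. The abstract does not mention power, and the 80% appears only in the Best Practices calculation.
- A reader might notice that Schoenfeld's formula gives 66 events in total for HR 2.0 and conclude that an event count was copied in as an arm size. The article gives no event count. Freedman's formula gives 71, which happens to equal the correct arm size, so such matches show nothing about origin.
- A reader might fault the missing return-to-work proportion, or the missing size and power for each new intervention. A condensed article may leave these to fuller documents.

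**Conclusion.** The point holds as an inconsistency in the abstract. The arms of 66 and 66 contradict the total of 142 in the same sentence and agree with neither 60 nor 71 per arm from the Sample size section. The calculation from 120 to 142 is sound, so the error lies in the abstract's split. The abstract also generalises to all five interventions a number that the body derives for two.

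The practical size is modest: ten participants per comparison on paper and, if 132 were recruited, about 112 instead of 120 after dropout, with 2 to 3 points of power lost. The power figure assumes equal arms, a two-sided test, no information from dropouts, and that 120 gives 80% power. The contradiction in the arm sizes needs only the assumption of equal arms, which the abstract itself implies. It should be corrected because a stated sample size that disagrees with its own calculation is wrong as written.

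**What to change.** Correct the abstract sentence in two respects.

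1. Give arm sizes that add to 142: 71 per arm if allocation is 1:1, corresponding to 120 (60 per arm) after 15% dropout. If 66 per arm was in fact the working target, the sponsor should say so and reconcile it with the Sample size section.
2. Limit the 142 to the two Best Practices, or confirm that it also applies to the three newly developed interventions.

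This is a change of wording. It requires no participants beyond the 142 already stated and no change to the analysis.

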**Discussion:**

The CASE-study is the first to conduct economic evaluations of multiple different employability interventions based on a similar methodological framework. The cost-effectiveness results for every employability intervention will be published in 2014, but the methods, strengths and weaknesses of the study protocol are discussed in this paper. To contribute to treatment options in occupational health practice and enable the development of guidelines on how to conduct economic evaluation better suited to this field; this paper provides an important first step.

**Trial registration:**

Four trials involved in the CASE-study are registered with the Netherlands Trial Registry: Care for Work (NTR2886), Health and Motion (NTR3111), Guidance to Excel in Return to Work (NTR3151), Care for Companies/Second Care (NTR3136).

## Background

### Work disability

Many recent studies have focused on reduced productivity and work absence due to work disability in Western countries [1-5]. Work disability prevents or detracts the employee's productivity and has many economic and public health consequences, such as problems for employers, employees, their families, and society [6-8]. In Western countries its main consequences are financial, due to reduced productivity, increased job turnover and the cost of additional rehabilitation programs [9-11]. In order to estimate the costs of work disability, staff absence and presence needs to be recorded. Absenteeism refers to the total days lost from work. Presenteeism refers to attending work whilst still stick or disabled, causing reduced productivity while at work [12]. Absenteeism and presenteeism can be used as integrated measures of physical, psychological and social functioning in studies of working populations [12,13]. In the Netherlands, the Sickness Absence Reduction Act was introduced in 1994 in an attempt to reduce absenteeism. Although there has been a major reduction in absenteeism, nearly 3 million Dutch workers still suffer from one or more chronic conditions which constrains their work performance [14]. Sickness absence remains a large problem in terms of costs, labour participation and social consequences [11,15,16]. The most common causes of sickness absence are: musculoskeletal complaints, mental health problems, and cardiovascular diseases [17,18]. Chronic diseases are more common among workers of 45 years and older, and it is expected that this age group will greatly increase, leading to a growing number of occupational health problems [17,18]. In the Netherlands, the total annual costs of absenteeism arising from health complaints and work disability amounted to 26 billion Euros, which accounts for almost 5% of the gross national product [14]. Additionally, Kremer and Steenbeek (2010) have computed that approximately 21.5% of absenteeism from work could be avoided if health services and employer and employee opportunities improved. To do this, shorter referral times, swifter medical care, improved collaboration between health care providers, reduced workload and an improved work-life balance are important factors [17,18].

### Return-to-work

Different return-to-work (RTW) interventions have been developed and evaluated to reduce sickness absence due to work disability. The effect, and occasionally the cost-effectiveness, of RTW interventions have been demonstrated in several observational studies [19-24], randomized controlled trials [25-30] and reviews [31,32]. For example, Franche et al. [31] concluded that work-based RTW interventions among employees with work-disability caused by musculoskeletal or other pain-related conditions can reduce work disability duration and associated costs. Lambeek et al. [33] showed that an integrated care programme for work-disabled participants with chronic low back pain has the potential to significantly reduce societal costs and improve care effectiveness, quality of life and function on a broad scale [33]. Other studies demonstrate that implementing preventive interventions before sickness absence occurs can be successful in preventing long-term sickness absence [19,29,34,35]. Whilst these results are very promising for society, participants, and employers, more research is necessary to confirm the long-term effects and cost-effectiveness of such interventions. However, methodological limitations in the current literature make it difficult to assess the feasibility of the different interventions proposed. These limitations include restriction of the population of interest due to the strict inclusion criteria, restrictions in the nature of the intervention evaluated, restrictions in study-design and the measurement of outcomes. There is moreover, a lack on transparency and consensus about how to conduct trial-based economic evaluations within the general field of employability.

### Objectives

This paper is the first of its kind to describe a transparent, uniform methodological design for the economic evaluation of several different trial-based interventions in the field of employability, disability and return-to-work. Known as the 'CASE-study' (Cost-effectiveness Analysis of Sustainable Employability), the project's aim is to evaluate at least five different employability interventions. All of the interventions share the common aim of reducing absenteeism and optimising the employability of employees with a known disability or those at risk of disability due to musculoskeletal complaints, mental health problems or a combination of both musculoskeletal and mental health complaints. In contrast with previous studies, the project design has no population restrictions and allows for the economic evaluation of any employability intervention regardless of the population they were developed for. Furthermore, the project also includes interventions provided in the primary and specialist health sectors as well as those delivered within the workplace. It also includes interventions aimed at reducing health care costs, wage replacement costs and other intervention costs in addition to improvements in return to disability duration and work return rates as measured by self-reported return to work dates, total duration of absence and subsequent recurrences, etc. Other outcomes include quality of life, quality of work life and general health status, etc. In addition, we cast a wide net to include a range of study designs since RCTs are not always possible in the economic evaluation of employability interventions. This paper describes the patient inflow in the event of an RCT or a quasi-experiment with a matched controlled design being conducted. For every employability intervention, an effect study will be conducted. In addition, from a societal perspective, a trial-based economic evaluation for every employability intervention will be carried out in a consistent manner. The results of these analyses will be discussed elsewhere in the future, but we hypothesize that the employability intervention is preferable in terms of costs, effects and utility compared to usual care. This paper will therefore demonstrate the strength of the CASE-study project in prescribing a methodological design which allows for the assessment of several different types of employability interventions within varying populations.

## Methodology

### Methods/design

#### Organisation of the CASE-study

We will carry out an economic evaluation designed for at least five Dutch employability interventions. Those undertaking the evaluation are not connected with the organisations or individuals who have developed, or are in the process of developing the employability interventions so no competing interests arise. Within the CASE-study each existing or innovative intervention will be compared with usual care for work-disabled employees or those at risk of work disability due to medical restrictions. At the start of the CASE-study, nine programmes were interested in participating in the project. Unfortunately four programmes could not collaborate because they were unable to provide the minimum required number of participants eligible for the study, or could not provide a comparable control group. The remaining five employability interventions have the ability to comply to the minimal requirements and focus on primary care, secondary or specialist care, and/or on the interaction between the employer and employee. Two existing employability interventions (called 'Best Practices') and three newly developed employability interventions are included in the study. The employability intervention focussing on primary care aims to acknowledge the importance of employability in general practice. This intervention is under development at the University of Nijmegen (UMC St Radboud). The employability intervention in specialist care is being developed jointly by the VU University Medical Centre Amsterdam (VUMC) and the Institute for Health and Care Research (EMGO+) and focuses on employability among patients who suffer from rheumatoid arthritis. The third newly developed intervention aims at improving the interaction between the employee and his/her employer by appointing an independent mediator. The intervention is being developed by a separate team at Maastricht University. One of the 'Best Practice' interventions, developed by Health & Motion Nederland, offers patients with physical health complaints the ability to implement a range of exercises learned at the physiotherapeutic setting in their working environment by means of a workplace-intervention. The fifth and final intervention is developed by Second Care/Care for Companies (Best Practice) and aims at achieving sustainable employability among patients with physical and/or psychological health complaints using a multidisciplinary approach. An overview of these interventions is provided in Figure 1.

**Figure 1 F1:**
[figure not shown]
**Employability interventions included in the CASE-study**.

It is beyond the scope of this design article to describe the precise content of each employability intervention in detail. This will be done when the results of the economic evaluation per employability intervention are published. What is of importance in this paper is that the employability interventions use an innovative, systematic approach in order to support work participation in employees with health complaints. These are innovative because both the healthcare system and the private/work life of the employees are considered in the intervention. The features of the interventions differ according to the patient population, but the aim remains the same: to reduce sickness absence and increase the potential of achieving sustainable employability.

The protocol for this study has been approved by the Ethics Committee of Psychology (ECP107) at Maastricht University, the Netherlands.

#### Usual work resumption care in the Netherlands

The Gatekeeper Improvement Act stipulates that the responsibility for work resumption lies with the employer and the employee. The employer is obliged to start an employee's work resumption programme as quickly as possible, so the employee can resume his/her own work or other adequate work. In return, the employee should accept the work activities the employer provides. Furthermore, and unique in the world, the Dutch reintegration process provides the employer with salary and mandatory reintegration obligations for a period of two years [36]. Participants included in the care as usual group will continue to receive care for their health complaints, but attention to work-related factors influencing these will only occur minimally. Nevertheless, since attention to labour and health-related characteristics is obligatory under the Gatekeeper Improvement Act [36], participants in the care as usual group who are work-disabled will also receive adequate care (care as usual). Participants included in the control group will be treated and supervised according to good clinical practice based on the evidence-based guidelines of the Dutch association of occupational physicians [37,38].

#### Participants

Employees eligible for participation in the study will be work-disabled or at risk of work disability due to medical restrictions. In order to identify these employees, we will use employer registration forms, registrations with health care organizations and insurance companies, and registration forms from those providing the intervention. Employees eligible for inclusion will be 18 to 63 years of age, perform paid labour for at least 12 h per week, and are able to communicate in Dutch. Reasons for exclusion are absenteeism for 1.5 years or longer, fulltime students with a student job, informal caregivers and/or volunteers.

In order to recruit a sufficient number of eligible employees, one or more health care providers providing an employability intervention will screen service users for inclusion in the study. When appropriate, information on the research will be provided to the patient. This will be done orally by the health care provider, possibly supported by a handout containing contact information for the researchers, what is expected of participants, privacy concerns, and so on. A self-completion card will be attached to each flyer (handout) consisting of a short checklist for inclusion and informed consent form for signing. The employee is requested to fill in the short checklist, sign the informed consent form, and send these back to the researcher. Participants will have at least 1 week to consider their participation in the study before signing the informed consent form. Participants will be screened for exclusion by the researcher on the basis of answers provided on the checklist. If an employee meets all the selection criteria and is willing to sign the consent form, randomization or matching will then place. Before the intervention starts, the first (baseline) measurement occurs. An email with a login code is sent to all participants, and they will be asked to fill in the baseline questionnaire. The questionnaire for the intervention group is identical to the one for the control group.

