### Effect evaluation

#### Primary outcome measure

The primary outcome measure in the CASE-study is reduced sickness absence duration in calendar days. Reduced sickness absence will be measured subjectively via patient self-report records. The duration of sick leave will be calculated as the time in calendar days since reduced productivity occurred (baseline). This will then be compared with the productivity time of a person at 6, 12, and 18 months. The success of an intervention will be defined by comparing the average reduction in sickness absence between the intervention group and the control group. The employability intervention is effective when the employees in the intervention group return to work twice as quickly as employees in the control group. Data on sickness absence duration will be gathered by using the productivity and disease questionnaire (PRODISQ) [45].

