### Data analyses

#### Effectiveness

All statistical analyses, performed to distinguish differences between the control group and the intervention group, will be performed according to the intention-to-treat principle. This means that the participants will remain in the group they were allocated to at baseline. All data regarding primary and secondary outcomes will be analysed using descriptive statistics. To control for protocol deviations likely to cause bias, data will be analyzed using per-protocol analyses whereby outcomes will be compared between those participants who received at least one or a partial intervention session and the control group. With the aim of correcting for possible regression to the mean, the baseline value of the particular outcome variable will be added to the model. Days of sick leave in the year before the inclusion, measured at baseline, will be added as a potential effect-modifier.

Diagnosis and prognostic parameters can be confounders, thus the Cox regression analysis for confounders will be used to adjust for differences between control and intervention groups. If necessary, differences in baseline will be adjusted for prognostic dissimilarities. Missing data will be handled using SPSS missing value analysis on item level. Completely missing measurements will be handled using multiple imputation.

The primary dependent variable is days of absence from work. In order to estimate the number of absence days, survival analyses will be used. There are two reasons why we opted to use survival statistics. Firstly, the time to sustainable employability is unlikely to be normally distributed which will make parametric statistical analysis difficult or inappropriate. Increasing productivity can occur quite early, possibly within months, but can also, as expected in the care as usual situation, may not be prolonged or may even decrease again. Secondly, survival analysis accounts for dropout by the technique of censoring. Participants who drop out will have the same hazard of sustainable employment than those that remained in the study. The Cox Proportional hazard model will therefore be used to analyse the HR of the days of sick leave duration. Reduced sickness absence duration in calendar days will be analysed with the Kaplan Meier survival method, and the differences in absence duration between both groups will be tested with a log rank test.

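### The primary analysis of time to return to work does not fit a population that includes employees who are only at risk and may not be absent at baseline

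*Protocol article*

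**What the plan says.** **Population.** The abstract admits employees "at risk of work disability, or already work-disabled due to medical restrictions", and the Participants section repeats both groups: "Employees eligible for participation in the study will be work-disabled or at risk of work disability due to medical restrictions". The only absence criterion is an upper bound: "Reasons for exclusion are absenteeism for 1.5 years or longer". Being absent at entry is not required.

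**Outcome.** Under Primary outcome measure: "The primary outcome measure in the CASE-study is reduced sickness absence duration in calendar days". The time origin follows: "The duration of sick leave will be calculated as the time in calendar days since reduced productivity occurred (baseline"). Success means that "employees in the intervention group return to work twice as quickly as employees in the control group". The same paragraph also compares the groups on average reduction in absence.

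**Analysis.** Under Data analyses, Effectiveness: "In order to estimate the number of absence days, survival analyses will be used". Kaplan-Meier, a log-rank test and a Cox model are named, under intention to treat. The justification there speaks of time to sustainable employability, and it expects that productivity gains may reverse.

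**Sample size.** For the existing Best Practices only: "we expect that a Hazard Ratio (HR) of 2.0 indicates a relevant difference in the average number of hours/days of lost work" after 18 months. With 80% power at the 0.05 level this gives 120 employees, or 142 after 15% dropout. The three new interventions were sized separately.

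**Relapse.** Under the secondary outcome Sustainable employability, more than fourteen consecutive days of absence after the intervention counts as failure.

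**The concern.** A survival analysis needs an origin, an event and a risk set that each analysed person can belong to. An employee who is working at baseline has no sick-leave spell whose end can be timed. Such a person could be left out, given duration zero, censored, or entered when a later absence begins. These choices give different answers, and the article picks none. Allocation is unblinded throughout and non-random in the matched designs, so leaving the choice until data are in hand is a real exposure.

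Two features of the endpoint make this worse. The origin equates onset of reduced productivity with baseline, although someone already absent for many months may enter; for that person the two dates can lie more than a year apart. The quantity also shifts between days of absence, average hours or days lost, return to work and sustainable employability. A hazard ratio for return to work is not a difference in average days lost.

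At stake are a primary result that is not uniquely defined and, where the power statement applies, a power figure that has not been shown for the people to be enrolled. Preventing new spells, which is the natural aim in at-risk employees, is not what the primary test measures.

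**Working it through.** **Inputs from the article:** hazard ratio 2.0, alpha 0.05 (taken as two-sided, since sidedness is not stated), power 80%, 120 evaluable, dropout 15%, roughly equal groups, 18 months. **Not given:** the event proportion and the share *f* of participants not absent at baseline. Both are assumptions below.

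**Step 1, the plan's figures.** Dropout: 120 / (1 − 0.15) = 141.2, so 142, as stated. Events by Schoenfeld: 4 × (1.960 + 0.842)² / (ln 2)² = 65.3, so 66. The 120 cannot be reproduced from the stated inputs alone; it is compatible with 66/120 = 55% having the event. Freedman's formula gives 71 events, or 59.2%.

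**Step 2, at-risk employees left out.** If the rest keep the 55% proportion, events = 66 × (1 − *f*) and power = Φ(√(events/4) × ln 2 − 1.960).

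| *f* | Events | Power |
|---|---|---|
| 0 | 66 | 80% |
| 10% | 59.4 | 76% |
| 20% | 52.8 | 71% |
| 30% | 46.2 | 65% |
| 50% | 33 | 51% |

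Starting from 71 events, the same formula gives 83% at *f* = 0, 79% at 10%, 74% at 20%, 69% at 30% and 54% at 50%.

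**Step 3, at-risk employees counted as returned on day 0.** With proportional hazards and hazard ratio 2.0, let *s* be the control proportion not returned by 18 months. Then (*s* + *s*²)/2 = 0.45, so *s* = 0.572. Return by 18 months is 43% in controls and 1 − 0.572² = 67% with the intervention. Simulation with 60 per arm, exponential times, and a share *f* of each arm given an event at time zero:

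| *f* | Estimated HR | Log-rank power |
|---|---|---|
| 20% | about 1.6 | roughly 60% |
| 30% | about 1.5 | roughly 45% |
| 50% | about 1.3 | roughly 25% |

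The power figures move by a few points with the simulation run and with whether the at-risk split is equal or random. A Cox Wald test loses more than the log-rank test when many events are tied at time zero (about 9% at *f* = 50% with an equal split). The log-rank figures are used here because that is the named test.

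**Step 4, how far the loss could be absent.** If every employee who is absent at baseline returned within 18 months, 66 events would still occur with *f* up to 1 − 66/120 = 45%. So the loss depends on the event proportion as well as on *f*.

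**The case against.** The strongest reply is that the article's wording is wider than return to work. If the clock starts at reduced productivity and the event is sustainable employability, some employees who are still working could have both an origin and an event. That is fair, and it rules out the claim that no at-risk employee can ever contribute. But the article does not define the event that way, and its success criterion is explicitly return to work. The reply therefore confirms that the definition is unsettled.

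A reader might infer that the 80% power fails across the whole CASE-study. The article does not support that. The hazard ratio of 2.0 and the 120 apply only to the two Best Practices, the at-risk share in those populations is not given, and step 4 shows that the events could still be reached.

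A reader might also infer that relapse and prevention go unmeasured. That is too strong. Relapse is captured as a secondary outcome, sick-leave days enter the costs, average absence reduction is mentioned, and the model takes account of baseline value and prior-year sick leave. None of this repairs the primary test.

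Finally, this is an umbrella article, and handling specific to one intervention may be set out elsewhere. That would excuse missing detail. Here, however, population, outcome, test and effect size are all stated, for a design presented as uniform, and they do not fit together.

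**Conclusion.** The mismatch between the eligible population and the primary time-to-event analysis is established from the text. It concerns the shared outcome and analysis, so it reaches every intervention that enrols at-risk employees. The origin is also inconsistent for people who enter with long prior absence, and relapse counts only as a secondary outcome.

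The effect on power is conditional and concerns the two Best Practices only. Assuming a 55% event proportion among those absent, leaving out 10% to 50% of participants lowers power to about 76% to 51%. Counting them as day-0 successes takes the hazard ratio to about 1.6 to 1.3, and log-rank power to roughly 60% to 25%, for shares of 20% to 50%. These are ranges under assumptions and do not demonstrate a shortfall. What can be said without assumptions is that the calculation states no allowance for participants without an absence to end. The primary result is not uniquely defined as the plan stands, so this should be settled before analysis.

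**What to change.** 1. Set one time origin, baseline or study entry, which works in both the randomised and the matched designs. Carry absence before entry as a covariate; prior-year sick leave is already collected.
2. Define one return-to-work event.
3. Restrict Kaplan-Meier, log-rank and Cox to participants on sick leave at baseline, and restate the power on the events expected in that subset, giving the assumed event proportion and at-risk share.
4. In all participants, analyse total sickness-absence days over 18 months, counting new spells and relapses, with baseline adjustment.
5. State which of the analyses in 3 and 4 is primary.
6. Balance on absence status at entry. It is currently neither a minimisation factor nor a matching criterion. Record it on the inclusion checklist, because allocation precedes the baseline questionnaire; this also keeps the subset in 3 defined before allocation.

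**Cost.** One extra checklist item, revised wording and a less favourable stated power. If 80% power is wanted in the absent subset under the 55% assumption, recruitment would have to rise. For example, at a 20% at-risk share, 120 / 0.8 = 150 evaluable and 150 / 0.85 = 176.5, so 177 in total instead of 142.
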